## **B. THE 'HEALTHY TODDLER' INTERVENTION**

### ***Theoretical framework of the 'Healthy toddler' intervention***

While the 'BOFT+' intervention - as primary starting point - focuses on child rearing issues from birth on, the 'Healthy toddler' intervention - as primary starting point - focuses on the established key-behaviors related to child-overweight. These are:

1. Promotion of outside exercise, activity and play,
2. Promotion of having family breakfast daily,
3. Discouragement of sweet drinks, and
4. Discouragement of television viewing (Hirasing et al., 2005).

The approach applied is the social-ecological model (Green et al., 1996), which recognizes the importance of environmental and personal factors on health behavior.

This guided the development of the 'Healthy toddler' intervention in the recently finished ZonMw project # 4010.0033, named 'The start of healthy living'. In case of very young children, parents can be considered as the main mediators of the toddler's environment. Parents influence the social and physical environment through their general parenting style (Darling & Steinberg, 1993) and parental practices. Fostering an authoritative parenting style has shown to decrease food stimuli in home (Golan et al., 2006). Therefore, parental practices have to be addressed in order to change the toddler's behavior. Important determinants of parental behavior can be found in classical behavior change theories, such as the Theory of Planned Behavior (Ajzen & Madden, 1986) and Social Cognitive Models (Bandura, 1986), and include attitude, social support, self-efficacy, perceived barriers, knowledge, and awareness. Therefore, the aim of the 'Healthy toddler' intervention is to make parents aware of potential/future overweight related problems and be motivated to prevent the development of overweight in their children from early age on by improving the four key behaviors defined in the YHC-Overweight Prevention Protocol, through their parenting.

In the 'Healthy toddler' intervention, positive attitudes of the parents towards applying strict behavior and positive attitudes towards the specific, recommended, parental practices are being promoted. Furthermore, parents are supported to overcome barriers for not applying these practices, and parents learn specific skills in order to be able to change their parenting according to the recommendations of the YHC-Overweight Prevention Protocol (Hirasing et al., 2005).

According suggestions proposed by McGuire for successful communication, several steps have to be taken in order to achieve behavior change (McGuire, 1985). First, the topic at hand (i.e. prevention of potential/future overweight related problems from early age on) has to be brought to attention and made understood. Second, determinants of the behavior have to be changed, e.g. creating a positive attitude towards the recommended behavior, increase

self-efficacy to perform the behavior, in order to change behavior. Finally, behavior change has to be maintained using feedback and reinforcement. The 'Healthy toddler' intervention package follows this scheme by application of the different elements included in this intervention package (see below; also see Annex with overview of the 'Healthy toddler' intervention).

Briefly, the intervention package will be applied twice (at age circa 18 months and age circa 24 months) and consists of an E-health module and face-to-face counseling by the YHC-professional. At the first application, at child age of circa 18 months, the E-health module will be introduced to the parents along with the regular invitation for the scheduled YHC-visit. It brings the topic to attention of the parents prior to visiting the YHC-center in an understandable manner and makes parents aware of the potential/future problem. Results from the 'Healthy toddler' pilot study show that the majority of the parents indeed understands the message and thinks it is useful and applicable. During the subsequent face-to-face counseling at the YHC-center for which an extra 15-minutes has been allocated for this topic, the YHC professional increases knowledge, awareness, attitudes and self-efficacy with regard to strict parenting practices. The YHC professionals, specifically trained for this purpose (see below), will apply motivational interviewing, which has proven to be effective in changing health behaviors in various settings and has been adapted for this specific YHC application (Rollnick et al., 2005). Finally, a second element of the E-health module will be applied, i.e. a reminder circa one month after the YHC-visit to maintain the behavior change, using positive feedback and reinforcement.

At the second application of the 'Healthy toddler' intervention package at the child age of circa 24 months, this series of activities (E-health module prior to the YHC-visit, face-to-face-counseling at the YHC center, E-health reminder one month afterwards) will be repeated with a focus on behavior change maintenance, or, in the case of relapse, the same approach as applied at age of circa 18 months old. At age 24 months, 10-minutes extra time will be allocated for this specific topic during face-to-face counseling.

### ***The distinct elements of the 'Healthy toddler' intervention***

As specific YHC-visiting schemes vary by region in the Netherlands, some variation will be allowed regarding the age of the first (circa 18 months) and second (circa 24 months) application of the intervention package, with a minimum age of 14 months old.

\*\* The E-health module 1 month prior to YHC-visit (at child age circa 18 months)

Prior to the scheduled YHC-visit at child age of circa 18 months old, along with the regular invitation for the YHC-visit, after having obtained informed consent, parents are invited to complete an E-health module. In 2007, circa 80% of Dutch households of 25-45 year olds have Internet access (CBS, 2007). Therefore, in the context of this study, we have decided that parents may decide themselves whether they gain access to the E-health module through Internet with immediate online tailored feed-back, or whether they use the E-health

module by mailed materials (after data-entry of the questionnaire upon receipt, the tailored feed-back will be mailed back to their homes directly).

The E-health module assesses the four priority behaviors defined by the YHC-Overweight Prevention Protocol, the general attitudes of the parents toward overweight prevention from early age on, and whether parents apply the recommended behavior specific parental practices. Participants will receive feedback tailored to their personnel situation given the provided answers posed by the E-health module (online or by mail if parents prefer so). As part of the tailored feedback, current behavior will be compared with the recommendations for each of the four priority behaviors. This will increase knowledge of the recommendations and make parents aware of their child's behavior. Additionally, parents will receive tailored advice on how to change their child's behavior, taking into account the recommended behavior specific parental practices (e.g. setting rules) (Hirasing et al, 2005).

The information entered by the parents regarding the four target behaviors and a summary of their attitudes generated by the E-health module will be sent to the YHC professional prior to the visit, enabling the professional to use this information in the counseling.

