**TIME SCHEDULE IN MONTHS**

The schedule below is provided in months from the start of the project, which is scheduled at July 1, 2008.

0-6: Recruiting 45 YHC-centers, preparing procedures/measures/protocols, and (start of) training of YHC-professionals regarding 'BOFT+' (15 YHC-teams) and the 'Healthy toddler' (15 YHC-teams) interventions.

6-18: During a year 3.000 parents of newborns will be provided information about the study and will be asked informed consent by 60 YHC-teams (expected participation rate at least 50%).

6-19: After recruitment of 1.500 parents/newborns, baseline measurements (T0 at child age 1 month) will be performed in the 3 study arms.

6-19: In the 'BOFT+' study arm (15 YHC-teams) the 'BOFT+' intervention will be started regarding 500 parents/newborns at child age 1 month.

12-24: Measurements at child age 6 months in 1.500 parents/infants (T1).

21-33: Measurements at child age of 15 months in 1.500 parents/infants (T2).

23-37: In the 'Healthy toddler' study arm (15 YHC-teams) the first part of the 'Healthy toddler' intervention will be applied to 500 parents/toddlers at child age of circa 18 months.

29-43: In the 'Healthy toddler' study arm (15 YHC-teams) the second part of the 'Healthy toddler' intervention will be applied to 500 parents/toddlers at child age of circa 24 months.

30-42: In the 'BOFT+' study arm (15 YHC-teams) the last scheduled contact moment between YHC-team and parents regarding the 'BOFT+' interventions will take place regarding 500 parents/toddlers at child age 24 months.

42-54: Measurements at child age of 36 months in 1.500 parents/infants (T3).

6-55: Data entry, and data cleaning.

18-60: Analyses, dissemination of the results.

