**POWER CONSIDERATIONS AND DETECTABLE DIFFERENCES**

We expect to receive complete data of 1.050 parents/toddlers at follow up at age 36 months old, equally divided over the 2 intervention groups and the control group. We assume equal standard deviations in the intervention groups and the control group, alpha of 0.05 and power of 0.80. We applied a correction factor to account for the cluster design, assuming an average cluster size of 23,3 toddlers (1.050/45) and an intra-class correlation coefficient of 0.10. For this expected sample size and assumptions, we calculated minimal detectable differences between an intervention and the control group at follow-up. We applied standard deviations and proportions/percentages reported in the literature or currently available data from the prior ZonMw projects (# 50-50140-98; # 4010.0033).

Target behaviors at age 36 months old:

Regarding the mean number of the reported minutes of physical activities of the children per day at age 36 months old, the study can detect a difference between intervention/control group of 18 minutes/day (SD=52 min/day). Regarding the mean consumption of sugar-sweetened drinks in glasses per day, a difference of 0.5 glasses/day (SD=1.5 glasses/day) can be detected. Regarding the mean number of minutes of TV viewing per day, a difference of 11 minutes/day can be detected (SD=32 minutes/day).

BMI at age 36 months old:

A difference of 0.44 BMI points between the mean BMI in the intervention group and the mean BMI in the control group at age 36 months can be detected by the study (SD=1.3) (Atkin & Davies, 2000).

Since we will use repeated measures (at age 15 months respectively 24 months in addition to 36 months) as covariates in the analyses, the power will be higher than indicated, which will facilitate the exploration of interaction effects of child gender, social disadvantage, ethnic background, and parental overweight status.

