#### T2. DATA COLLECTION AT CHILD AGE 15 MONTHS

The following data will be collected at child age 15 months (T2).

- Weight and length of the child (from YHC-file at age 14 months);
- History of breast/bottle feeding; supplemental feeding/introduction of solid food;

- Energy balance-related behaviors ('BOFT' behaviors): exercise and outdoor playing, having an appropriate family breakfast daily, sugar sweetened drinks consumption, and TV viewing, measured by parental questionnaires (Raaijmakers et al., 2007);
- Attitudes, motivation and perceived control of parents regarding the four energy balance-related ('BOFT') behaviors (Raaijmakers et al., 2007);
- Child rearing questionnaire for parents; Opvoedingsvragenlijst Voor Ouders (OVO) (Dekovic et al., 1991);
- Parenting style (PS) (Arnold et al., 1993);
- Parenting practices and rules (PP) (Arredondo et al., 2006);
- Health and well-being of the child: brief-Infant-Toddler Social and Emotional Assessment (brief ITSEA) (Briggs-Gowan et al., 2004).

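### The permitted minimum age for the first Healthy toddler package (14 months) lets the 15-month T2 measurement fall after the intervention has started in that arm but not in control

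*Protocol*

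**What the plan says.** - **Age at first package.** Section 5.B (distinct elements of the Healthy toddler intervention) gives a nominal age but adds that "some variation will be allowed regarding the age of the first (circa 18 months", and closes the sentence with "application of the intervention package, with a minimum age of 14 months old".
- **Order within the package.** The same section starts the package before the visit: "The E-health module 1 month prior to YHC-visit (at child age circa 18 months". The module itself delivers tailored advice on the four behaviors and on parenting.
- **T2.** Section 6 states "The following data will be collected at child age 15 months (T2". The questionnaire covers the four behaviors, parental attitudes and the parenting instruments. The anthropometry comes from an earlier contact: "Weight and length of the child (from YHC-file at age 14 months".
- **Calendar.** The time schedule in Section 3 has "21-33: Measurements at child age of 15 months in 1.500 parents/infants (T2" and "23-37: In the 'Healthy toddler' study arm (15 YHC-teams) the first part".
- **Use in the analysis.** Section 4 (power considerations) says "Since we will use repeated measures (at age 15 months respectively 24 months in addition to 36 months) as covariates". Section 7 adjusts the multilevel models for baseline values.
- **BOFT+.** The time schedule starts this intervention at child age 1 month.

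**The concern.** T0 and T1 in Section 6 contain none of the four behaviors, the attitudes or the child-rearing, parenting-style and parenting-practice scales. For these outcomes a baseline value can only mean T2. That works for Healthy toddler versus control if T2 comes before the first module.

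The 14-month allowance breaks this order, and no section requires T2 to be completed before the first module or visit. Where a team uses the allowance, its parents answer T2 after receiving the tailored advice and possibly the counseling, while control parents answer it untreated. Adjusting for T2 then takes out part of the effect on primary behavioral outcomes, and the bias runs towards no effect. The mediation analysis in Section 7 would also lack parenting values from before the intervention in those teams.

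The case is not far-fetched. Section 5.B gives differing regional visit schemes as the reason for the allowance. The protocol itself points to a routine contact at 14 months, both in the T2 weight and length and in the BOFT+ scheme (Figure 2).

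**Working it through.** **1. The plan's calendar.** Recruitment runs in project months 6 to 18. A measurement at child age *a* therefore falls in months 6 + *a* to 18 + *a*.

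| Event | Age (months) | Computed window | Stated window |
|---|---|---|---|
| T2 | 15 | 21–33 | 21–33 |
| First package, nominal | 18 | 24–36 | 23–37 |
| First package, minimum age | 14 | 20–32 | none |
| E-health module for a 14-month visit | 13 | 19–31 | none |

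The T2 window is reproduced exactly. The stated 23–37 corresponds to ages 23 − 6 = 17 to 37 − 18 = 19 months. A 14-month application would open in month 20, three months before the scheduled window.

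**2. Order for one child.** If 14 months refers to the visit, the module falls at about 13 months and the visit at 14, so both precede T2. If it refers to the module, the module precedes T2 by about a month and the visit is level with it. On either reading at least the module comes before T2.

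**3. Effect of adjusting for T2.** Let δ be the 36-month effect, ρ the within-arm slope of the 36-month value on T2, p the share of the Healthy toddler arm treated before T2, and f the fraction of δ already present at T2 in those families. The arms then differ at T2 by p·f·δ, and the adjusted estimate is expected to be

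δ − ρ·(p·f·δ) = δ(1 − ρ·p·f).

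The protocol gives none of ρ, p or f. Assuming ρ = 0.3 to 0.7 and f = 0.5 to 1:

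| p | Smallest loss | Largest loss |
|---|---|---|
| 0.10 | 0.3 × 0.10 × 0.5 = 1.5% | 0.7 × 0.10 × 1 = 7% |
| 0.25 | 0.3 × 0.25 × 0.5 = 3.75% | 0.7 × 0.25 × 1 = 17.5% |
| 0.50 | 0.3 × 0.50 × 0.5 = 7.5% | 0.7 × 0.50 × 1 = 35% |
| 1 (upper bound) | 0.3 × 1 × 0.5 = 15% | 0.7 × 1 × 1 = 70% |

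**4. The other covariates.** BOFT+ starts at 1 month, so T2 comes 14 months after its start for every BOFT+ child. The 24-month measure named in Section 4 follows the start of both interventions. Section 6 lists only weight, length and waist circumference at 24 months, so that covariate concerns body size.

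**The case against.** Fourteen months is an outer limit on tolerated variation. Elsewhere the protocol puts the first Healthy toddler package at about 18 months, and the time schedule gives one window for all 15 teams that fits only about 17 to 19 months. This stands as evidence that T2 was meant to come first, and it confines the problem to early-visit teams. It does not remove the written permission.

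The protocol names T0 as baseline and never labels T2 pre-intervention. That is true, but T0 and T1 lack these outcomes and Section 4 plans the 15-month value as a covariate.

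Three stronger readings are tempting and not supported:

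- **Only the Healthy toddler arm is affected.** This is false across three arms. In BOFT+ the problem is certain; in Healthy toddler it is possible. The contrast holds only against control.
- **Power drops sharply.** With 350 per arm and a design effect of 1 + (23.33 − 1) × 0.10 = 3.233, the effective number is 108.2 and the standard error √(2/108.2) = 0.136 SD. The effect detectable with 80% power (two-sided 5%) is 0.381 SD. Assuming p = 0.3, ρ = 0.5 and f = 1, it shrinks to 0.381 × 0.85 = 0.324, and power appears to fall to Φ(0.324/0.1359 − 1.96) = 66%. But the attenuation arises only if T2 is adjusted for, and adjustment also reduces the standard error. With correlation 0.5 at both levels it becomes 0.1359 × √0.75 = 0.1177, and power is about 79%. Full effect at T2, before the second package, is also an extreme assumption.
- **All primary outcomes suffer alike.** T2 weight and length come from the 14-month file, so BMI is less exposed to this conflict than the questionnaire outcomes.

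**Conclusion.** The concern holds as an ordering conflict between the minimum age in Section 5.B, the fixed age of T2 in Section 6 and the time schedule in Section 3. Followed as written, the plan can adjust Healthy toddler versus control for a value measured after the intervention began in one of the two arms. The consequence is attenuation, not a demonstrated loss of power.

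The size cannot be fixed from the protocol, because the share of teams with an early visit is not given. Under the assumed slopes and fractions, the loss is minor at a 10% share and could be material from a 25% share upwards. Separately, and whatever the visit ages, T2 in BOFT+ and the 24-month measure in both intervention arms fall after intervention start and are not baseline values.

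**What to change.** 1. Reconcile the minimum age in Section 5.B, the time schedule in Section 3, T2 in Section 6, the covariate sentence in Section 4 and the model in Section 7. Which application age applies is for the investigators to settle.
2. State that in each service the T2 questionnaire is sent and due before the first E-health invitation, at the same child age in all three arms of that service.
3. Where a service's schedule makes this impossible, do not use T2 as a baseline covariate for any arm of that service. Decide this from the schedule, not from each family's return date; otherwise covariate use would depend on behavior after randomization.
4. Do not adjust the effect estimate for any measure taken after intervention start: T2 in BOFT+, and 24 months in both intervention arms. Use earlier covariates (T0 and T1 for Healthy toddler versus control; T0 for BOFT+, since T1 at 6 months also follows its start), or model the later values as repeated outcomes.

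The cost is mainly the mailing dates of an existing questionnaire. T2 age would vary between services; for a 14-month visit, T2 would be due before about 13 months, more than two months early. Some covariate precision is lost, chiefly for the behaviors, which T0 and T1 do not measure.

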**\*\* Face-to-face counseling at the YHC-center (child age circa 18 months)**

During the regular visit of parents and their (circa) 18 months old toddler to the YHC center, the YHC professional will apply the Overweight Prevention Protocol and make use of available information from the E-health module. The face-to-face consultation regarding overweight prevention will be performed by a trained YHC-professional of the intervention-team. At this first time face-to-face counseling at the YHC-center, 15 minutes extra time will be allocated for this topic in the context of the regular YHC visit (including measurements for the purpose of the evaluation) (see Korfage et al, 2002).

The Overweight Prevention Protocol consists firstly of a structured assessment of the four priority energy-balanced behaviors. In the face-to-face counseling, the trained YHC-professional will, according to the YHC-Overweight prevention protocol, apply motivational interviewing to promote daily exercise and outdoor playing time, having a family breakfast daily, lessening sugar sweetened drinks, and limiting TV time (in Dutch 'BOFT' behaviors) (Hirasing et al., 2005). See below regarding the training of the YHC-professionals in this Intervention group.

During the counseling, the YHC-professional will motivate parents to prevent the development of overweight in their child while it grows up. The YHC-professional will make parents see advantages of applying strict parental practices, and correct false assumptions parents have with regard to applying strict rules. Additionally, he or she will help identifying barriers experienced by the parents preventing them to perform the preferred parenting behavior and provide a different perspective on the barrier in order to overcome the obstacle.

Self-efficacy will be improved by providing them with skills to apply strict parental practices (Sanders et al., 2003; West, 2005).

Parenting skills that the YHC professional will include in the counseling interview are: establishing eating routines by setting specific times for meals and snacks, especially for having breakfast daily; reducing extra foods such as sugar sweetened beverages; provide healthy alternatives, like fruits and low fat/sugar foods; demand daily consumption of fruit and vegetables, limit sedentary activities by setting rules about TV viewing and increase physical activity by active family leisure time and active transport (Hirasing et al, 2005).

**\*\* E-health module reminder 1 month after YHC-visit**

Circa one month after the face-to-face counseling at the YHC-center, parents will receive an electronic (or paper version if they prefer so) reminder regarding their tailored advice; including the tailored advice with regard to behavior specific parenting practices.

**\*\* Repetition of the 'Healthy toddler' intervention package at child age (circa) 24 months**

The above-described distinct elements of the 'Healthy toddler' intervention package will be applied again at the age of (circa) 24 months. The E-health module, one month prior to the second counseling on this topic at the YHC-center, can assess if behavior change was achieved and provide positive feedback and reinforcement if this was the case. If not, parents will again receive tailored advice on how to achieve behavior changes. During the second-time face-to-face counseling regarding this topic, the YHC professional will assess if behavior change was maintained. If this was the case, the YHC professional will provide positive feedback and reinforcement. If behavior change was not achieved or parents reported relapse, the YHC professional will assess what causes the relapse and again apply the same counseling strategy, based on a motivational interviewing approach, as described above.

At this second time face-to-face counseling at the YHC-center, 10 minutes extra time will be allocated for this topic in the context of the regular YHC visit (including measurements for the purpose of the evaluation) (see Korfage et al, 2002).

The E-health reminder circa one month after the second face-to-face counseling, will also be used for either positive feedback, or provision of tailored advice.

Figure 3. ***Flowchart of the 'Healthy Toddler' Intervention***

| Steps according Persuasion-Communication Model (McGuire, 1985)                                                                                            | Element of the 'Healthy Toddler' intervention Package                | Content / activities                                                                                                                                                                                                                                                                                                                                                                                                                                                                                                                                                                                                                             | Age of the child |
|-----------------------------------------------------------------------------------------------------------------------------------------------------------|----------------------------------------------------------------------|--------------------------------------------------------------------------------------------------------------------------------------------------------------------------------------------------------------------------------------------------------------------------------------------------------------------------------------------------------------------------------------------------------------------------------------------------------------------------------------------------------------------------------------------------------------------------------------------------------------------------------------------------|------------------|
| Attention for the health message                                                                                                                          | E-Health Module                                                      | 
 
- Assessment of four key behaviours
 
- Assessment of parenting behaviour
 
- Feedback on four key behaviours, in comparison with recommendations
 
- Tailored advise, taking into account the four behaviours and parenting practices
 
                                                                                                                                                                                                                                                                                                                                    | ± 18 months      |
| Changing determinants and behaviour: 
 
- Attitude
 
- Self-efficacy
 
- Parenting behaviour
 
 | Counselling with motivational interviewing technique                 | 
 
- Making parents aware of their child's behaviour
 
- Motivate parents to prevent overweight in their child
 
- Stress the parents responsibility and importance strict parenting
 
- Motivate parents to change their parenting
 
- Discuss advantages of strict parenting
 
- Discuss potential barriers (e.g. time constraints)
 
- Improve self-efficacy
 
- Provide parents skills: 
 
- Setting rules, giving good example, use praise and award, do not use food as a means of control
 
 
 
 | ± 18 months      |
| Maintain behaviour change                                                                                                                                 | Reminder                                                             | Reminder of tailored advice from E-Health module
Positive feedback                                                                                                                                                                                                                                                                                                                                                                                                                                                                                                                                                                            | ± 18 months      |
|                                                                                                                                                           |                                                                      |                                                                                                                                                                                                                                                                                                                                                                                                                                                                                                                                                                                                                                                  |                  |
|                                                                                                                                                           | 2 nd E-health Module                                      | 
 
- Assessment four key behaviours
 
- Assessment of parenting behaviour
 
 
If behaviour change was achieved, parents receive positive feedback
 
If not, parents receive tailored advice
                                                                                                                                                                                                                                                                                                                                                                                        | ± 24 months      |
|                                                                                                                                                           | 2 nd Counselling with motivational interviewing technique | 
 
- Assessment of behaviour change
 
- if yes, provide positive feedback
 
- If not, repeat activities described in 1st counselling
 
                                                                                                                                                                                                                                                                                                                                                                                                                                     | ± 24 months      |
|                                                                                                                                                           | 2 nd Reminder                                             | Reminder of tailored advice from E-Health module                                                                                                                                                                                                                                                                                                                                                                                                                                                                                                                                                                                                 | ± 24 months      |

